#### Recruitment {15}

Adequate participant involvement will be achieved by enlisting the two main hospitals in the area that conduct PCI procedures.

### Assignment of interventions: allocation

#### Sequence generation {16a}

In both hospitals participating in the trial, all patients are randomly allocated to either the control arm or the active arm, as shown in Fig. 1. Randomization is computer generated in the cath labs of each hospital.

#### Concealment mechanism {16b}

Allocation of patients is computer generated and shown to the treating cardiologist on the morning of the PCI.

#### Implementation {16c}

[name] in the Section of Cardiology, King Fahd Hospital of the University and [name] [name] in the Department of Cardiology, King Fahd Armed Forces Hospital are responsible for allocation and enrollment of participants according to the design plan of the trial.

### Assignment of interventions: blinding

#### Who will be blinded {17a}

Both outcome assessors and data analysts are blinded to the data.

#### Procedure for unblinding if needed {17b}

Not applicable

### Data collection and management

#### Plans for assessment and collection of outcomes {18a}

The treating physician collects all the required data on prepared formats and subsequently these data are uploaded onto the clinical trial website of this study. For each patient, follow up data are collected one year after the date of PCI. In the Department of Internal Medicine in each of the two hospitals, two to three nurses have been assigned to monitor each patient included in the study and to note when each patient’s one-year follow up visit will be. Prior to the appointment date, the nurse informs the residents responsible for collecting the follow up data that the patient will be attending. The residents can also access the medical records of each patient to obtain a full history of the events for the 12-month period following the PCI. For accuracy, the entered follow up data are rechecked by a second resident against the medical records. In the event that a patient has no assigned follow up visit after a one-year period post PCI, the nurse will alert the residents who will then contact the patient and arrange for a follow up visit for the patient. Data collection forms can be obtained upon request from the corresponding author.

#### Plans to promote participant retention and complete follow-up {18b}

All participants are given a leaflet which explains the objectives, rationale, and importance of participating in this trial. The treating cardiologist explains that patient confidentiality is maintained during and after the trial and addresses any concerns the potential applicant may have and that the participant can withdraw from the trial at any time. The cardiologist also emphasizes the importance of attending scheduled appointments but will facilitate rescheduling appointments to provide flexibility. Outcome data of participants who withdraw from the trial are treated as confidential and at the end of the study the investigators will contact these participants to seek permission to include their data in the study.

#### Data management {19}

Patient data is compiled by a resident involved in the trial on the day the PCI is completed. The data are entered onto a hard copy data entry form. Subsequently, a second resident involved in the trial compares the data entry forms to the medical records. Any discrepancies are highlighted to the treating cardiologist and a decision is taken as to the correct data to be used. At King Fahd Hospital of the University, each patient’s data is uploaded into the Clinical trials.gov website by a resident and the accuracy of each entry is verified independently by a second resident in the Department of Internal Medicine who is not involved in the trial except for the purpose of reviewing the data. The original documents are kept in numerical order (coded number) in locked cabinets in the office of the principal investigator. These documents will be stored for a period of three years post completion of the study. The primary and secondary end points are adjudicated by a panel comprising the consultants and residents involved in the trial in each hospital.

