### Trial design {8}

This is the first multicenter RCT in the field of personalized cardiovascular medicine in the Middle East and aims to prove the value of bedside pharmacogenetic testing in approximately 1500 STEMI patients undergoing PCI. This study is a prospective parallel assignment trial, the aim of which is to determine whether prescribing prasugrel or ticagrelor, rather than clopidogrel, after primary PCI in carriers of *CYP2C19**2 LoF alleles is superior in reducing a net clinical benefit outcome consisting of cardiovascular death, myocardial infarction (MI), stent thrombosis, stroke and Platelet Inhibition and Patient Outcomes (PLATO) major bleeding. All patients aged between 18 and 70 years are eligible for inclusion. The sample size calculation is based on the estimated event rates for the primary net clinical benefit endpoint. The estimated event rate of the active arm is 9%, based on the recently published Patient Outcomes after primary PCI (POPular Genetics) trial and the Saudi Acute Myocardial Infarction Registry (STARS) [15–21]. The estimated event rate for the control arm is 13.6%, based on the PLATO trial [19, 20]. Using a power of 80% and an alpha level of 0.05, 1484 patients are required. Accounting for drop-outs 1500 patients will be included. Data are entered on http://www.openclinica.nl.

ST-segment elevation MI is defined according to the European Society of Cardiology and American College of Cardiology guidelines [8]. All demographic and clinical data are obtained for each participating patient from the medical records at the time of the index PCI. The treating physicians are not blinded to group allocation since the therapy could require alteration in patients with *CYP2C19*2* LoF alleles.

The Spartan RX device is being used to determine the *2 genotype of patients. The Spartan RX *CYP2C19*2* platform is placed in the catheterization lab of each hospital to enable immediate genetic testing. The trial was conducted in accordance with SPIRIT guidelines.

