### Eligibility criteria {10}

The consultants involved in the project, who are all in the Department of Internal Medicine (Cardiology), perform the interventions. The inclusion and exclusion criteria are listed below:

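### The statement that outcome assessors are blinded is not supported by the adjudication panel described, which includes consultants who know the arm of the patients they treated

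*Protocol article*

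**What the plan says.** All references are to the protocol article.

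- **Who will be blinded {17a}:** "Both outcome assessors and data analysts are blinded to the data".
- **Data management {19}:** "The primary and secondary end points are adjudicated by a panel comprising the consultants and residents involved in the trial in each hospital".
- **Eligibility criteria {10}:** "The consultants involved in the project, who are all in the Department of Internal Medicine (Cardiology), perform the interventions".
- **Trial design {8}:** "The treating physicians are not blinded to group allocation".
- **Concealment mechanism {16b}:** "Allocation of patients is computer generated and shown to the treating cardiologist on the morning of the PCI".
- **Item {18a}, on how outcomes are captured:** "The treating physician collects all the required data on prepared formats and subsequently these data are uploaded onto the clinical trial website of this study". Of the year after the index procedure it adds: "The residents can also access the medical records of each patient to obtain a full history of the events for the 12-month period following" […].

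Data management {19} adds that a trial resident compiles the data on the day of the PCI, and that discrepancies go to the treating cardiologist before the correct value is settled. The article describes no masked event packet, no exchange of cases between hospitals, and no rule that a clinician abstains on his or her own patients.

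**The concern.** The primary endpoint combines recurrent MI, non-fatal stroke, cardiovascular death and PLATO major bleeding (Outcomes {12}). Several of these need a judgement: whether a troponin rise is a new infarction, whether a death is cardiovascular, whether a bleed is major. In an open-label trial, masked adjudication is the main protection against that judgement following the arm. The article claims this protection, but the people it names as adjudicators overlap with those it declares unblinded. The claim would stand behind the primary result and would be repeated in the report of the trial.

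**Working it through.** **1. The passages side by side.**

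| Question | Answer in the article | Section |
|---|---|---|
| Who adjudicates? | Trial consultants and residents, in each hospital | {19} |
| Who are the consultants? | Those who perform the interventions | {10} |
| Do treating physicians know the arm? | Yes | {8}, {16b} |
| Are outcome assessors blinded? | Yes | {17a} |

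The first three answers put on the panel people who know the arm of at least their own patients. The fourth does not fit with them. The wording in {17a} is also loose: it speaks of blinding to data, not to allocation.

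**2. What the residents can know.** No section says that they know the arm. They read the medical records, which would be expected to show the P2Y12 drug. Active-arm non-carriers take clopidogrel, as controls do. With the article's carrier figures of about 26% (Abstract, Background) or about 20% (Abstract, Discussion), and assuming 750 per arm, carriers in the active arm number 0.26 × 750 = 195 or 0.20 × 750 = 150. About 74% to 80% of the active arm would then be on the control drug. Prasugrel or ticagrelor suggests the active arm. So would a genotype result filed during follow-up, because controls are genotyped only at the end of the study ({6b}).

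**3. The plan's own figure.** Inputs from Sample size {14}: 13.6% control, 9% active, 80% power, alpha 0.05. Two-sided testing and 1:1 allocation are assumed.

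n per arm = [1.96·√(2·0.113·0.887) + 0.842·√(0.136·0.864 + 0.09·0.91)]² / 0.046² = 742.4, so 743 per arm and 1486 in total. The article states 1484, so its figure reproduces. With 750 per arm, the planned events are 750 × 0.136 = 102 and 750 × 0.09 = 67.5, about 170 in all.

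**4. Illustration of size.** The shifts are assumptions; the article gives no figure for misclassification. Take no true effect, a common event rate p, 750 per arm and a pooled two-proportion test. Move k events out of the active arm and, in the two-arm scenario, k into the control arm.

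- Two-arm difference: d = 2k/750. For k = 5 this is 1.33 points (1.33/4.6 = 29% of the planned difference). For k = 10 it is 2.67 points (58%).
- Active arm only: d = k/750, that is 0.67 or 1.33 points.
- Chance of a significant result favouring the active arm: Φ[(d − 1.96·SE₀)/SE₁], with SE₀ pooled and SE₁ unpooled.

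Example, p = 0.113, k = 5, both arms: SE₀ = 0.01635, SE₁ = 0.01635, so Φ[(0.01333 − 0.03204)/0.01635] = Φ(−1.14) = 12.6%.

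| Common rate | None moved | 5 per arm, both | 10 per arm, both | 5, active only | 10, active only |
|---|---|---|---|---|---|
| 9% | 2.5% | 14.5% | 43.8% | 6.7% | 15.2% |
| 11.3% | 2.5% | 12.6% | 37.1% | 6.1% | 13.1% |
| 13.6% | 2.5% | 11.4% | 32.5% | 5.7% | 11.7% |

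Separate calculations, including a simulation, agree with the entries they cover to within one percentage point.

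**The case against.** The strongest reply is that the text unblinds each treating physician for his or her own patients and no further. Panel members who did not treat a patient could be masked to that patient's arm. The article condenses a fuller protocol, which may provide for masked packets or abstention. A reader might infer that every adjudicator knows every patient's arm and that the blinding statement is simply false. The article does not support that: knowledge is explicit only for treating consultants, and for residents it is inferred from records in which the drug often does not separate the arms.

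This narrows the point but does not remove it. The article positively states who adjudicates and who is blinded, so this is a conflict between statements and not a missing detail. Masked paper alone would not blind a consultant who treated the patient.

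A second reply concerns direction. The investigators expect a net benefit in the active arm (Abstract, Discussion), so a reader might infer bias in its favour. But they also expect more bleeding with the alternatives (Primary objectives), and major bleeding is part of the primary endpoint. Expectation on that component runs the other way and could partly offset the rest. The published definitions cited in Outcomes {12} for cardiovascular death, MI and stroke also limit discretion without removing it. Both arguments stand.

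**Conclusion.** The blinding claim in {17a} is not supported by the panel described in {19}, and no other section repairs it. The two must be reconciled before analysis. Unmasked adjudication could bias the primary result; the article establishes neither that it does nor in which direction.

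The size depends on assumed shifts. If 5 events per arm move in opposite directions, the 2.5% chance of a false result favouring the active arm becomes about 11–15%; with 10 it becomes about 33–44%. If only active-arm events move, the figures are about 6–7% and 12–15%. All rest on no true effect, 750 per arm and a common rate of 9% to 13.6%. They show that a handful of reclassified events would matter; they do not estimate what will happen. The case for a change rests on the conflict in the text.

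**What to change.** - Have each hospital's existing panel adjudicate the other hospital's suspected events, from packets in which arm, genotype and P2Y12 drug name are masked.
- State that no physician votes on a patient he or she treated.
- Send every suspected event to the panel, including those later judged negative, so that selection before adjudication does not depend on the arm.
- Re-adjudicate events already classified in the same way before analysis. This is still possible: the article reports that recruitment is under way and analysis has not begun (Trial status; Data Availability).
- Reword {17a} to say who is blind to what. If masking cannot be done, withdraw the statement that outcome assessors are blinded.

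**Cost.** No new panel is needed, and treatment and sample size are unchanged. Staff at both hospitals must mask all suspected primary and secondary events, which is more than the roughly 170 planned primary events. The reviewing resident who is otherwise outside the trial is described only for King Fahd Hospital of the University, and only for data review. That role would have to be extended to preparing packets, and the other hospital must name someone for the same work.

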#### Confidentiality {27}

Personal information about potential and enrolled participants is collected and coded before being transferred to the clinical trial web site. All paper documentation related to this trial, including participant information, is stored in locked cabinets in the office of the principal investigator. Any documentation which can link the participant to the coded number is kept in a separate secured locked cabinet. Access to the clinical trial web site is restricted to the treating cardiologist and data entry personnel. This system is password protected.

#### Plans for collection, laboratory evaluation and storage of biological specimens for genetic or molecular analysis in this trial/future use {33}

Blood samples and buccal swabs collected from the control arm are stored at − 80 until analysis at the end of the one-year period.

### Statistical methods

#### Statistical methods for primary and secondary outcomes {20a}

All analyses will be carried out on an intention-to-treat basis. Binary and other categorical variables will be compared using χ^2^ test or Fisher’s exact test, as appropriate. For continuous data, two-sided unpaired student’s t tests will be used. Comparison between groups will be undertaken using Cox regression analysis. At the end of the study, cost-effectiveness and quality of life will be determined in the study groups by determining the quality-adjusted life-years, net cost per life year gained and net cost per quality-adjusted life-years. Cost-effectiveness will be estimated from societal and healthcare perspectives as described in the methods reported for pharmacoeconomic research [25]. Data will be analyzed using SPSS version 24.

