#### Outcomes {12}

The primary end point is the number of patients who develop an adverse major cardiovascular event which includes recurrent MI, non-fatal stroke, cardiovascular death, and PLATO major bleeding one-year post PCI. The definition of cardiovascular death, MI and stroke are as reported by Hicks et al., (2017) Cardiovascular and Stroke Endpoint Definitions for Clinical Trials [22]. Secondary outcomes within one-year post PCI include cardiovascular death, cerebrovascular death, death from recurrent MI, stroke, stent thrombosis, target vessel revascularization or a combination of the above.

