#### Sample size {14}

The sample size calculation is based on the estimated event rates for the primary net clinical benefit endpoint. The estimated event rate of the active arm is 9%, based on the recently published Patient Outcomes after primary PCI (POPular Genetics) trial and the Saudi Acute Myocardial Infarction Registry (STARS) [15–21]. The estimated event rate for the control arm is 13.6%, based on the PLATO trial [23, 24]. Using a power of 80% and an alpha level of 0.05, it is estimated 1484 patients are required to prove superiority of the genotype-guided strategy. Accounting from drop outs, 1500 patients will be included. Data are entered on http://www.openclinica.nl.

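### The analysis section names chi-square/Fisher and Cox without saying which is primary and states covariate adjustment for neither; prespecified adjustment would be a modest, nearly free efficiency gain

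*Protocol article*

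**What the plan says.** All of this is in the Protocol article.

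- **Endpoint.** Outcomes {12}: "The primary end point is the number of patients who develop an adverse major cardiovascular event which includes recurrent MI", together with non-fatal stroke, cardiovascular death and PLATO major bleeding at one year. This is a binary outcome per patient.
- **Analysis.** Statistical methods {20a}: "Binary and other categorical variables will be compared using" a chi-square or Fisher's exact test. Two sentences later: "Comparison between groups will be undertaken using Cox regression analysis". Neither method is labelled primary, and no covariates are mentioned for either.
- **Sample size.** Sample size {14} assumes 9% in the active arm and 13.6% in the control arm. "Using a power of 80% and an alpha level of 0.05, it is estimated 1484 patients are required". Then: "Accounting from drop outs, 1500 patients will be included".
- **Baseline data.** Trial design {8}: "All demographic and clinical data are obtained for each participating patient from the medical records at the time of the index PCI". No individual variable is listed as prognostic.

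**The concern.** A chi-square or Fisher test compares two proportions and cannot use what is known about each patient's risk at entry. Cox regression can, but the plan does not say that it will. If the recorded baseline data predict the one-year composite, an analysis that uses them estimates the same risk difference with a smaller variance and needs no extra patients or data collection.

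The margin is thin. The trial is sized at 80% power, and the allowance for drop-outs is 1500 − 1484 = 16 patients, or 16/1500 = 1.1%. Small gains in precision are therefore worth having. Leaving the primary method open also means that two between-arm results could each be presented as the main one.

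**Working it through.** **Inputs from the documents.** Control rate p₁ = 0.136, active rate p₂ = 0.09, alpha 0.05, power 80%, 1484 required, 1500 planned (Sample size {14}). **Assumptions.** The section states neither sidedness nor allocation ratio. I take two-sided and 1:1, because these reproduce the stated total.

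**Step 1: reproduce the plan's figure.** With p̄ = (0.136 + 0.09)/2 = 0.113,

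n per arm = [1.960·√(2p̄(1−p̄)) + 0.8416·√(p₁(1−p₁) + p₂(1−p₂))]² / (p₁−p₂)²

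= [1.960 × 0.4477 + 0.8416 × 0.4465]² / 0.046² = 742.4.

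That is 1484 at 742 per arm, or 1486 if each arm is rounded up. A one-sided test (1170) or a continuity correction (1572) does not match. The trial was therefore sized for an unadjusted comparison of two proportions.

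**Step 2: power as planned.** Power = Φ{[0.046·√n − 1.960 × 0.4477] / 0.4465}.

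- n = 742 per arm: 80.0%.
- n = 750 per arm: 80.4%.

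For Cox under proportional hazards, HR = ln(1 − 0.09)/ln(1 − 0.136) = 0.645. Expected events are 1500 × 0.113 = 169.5. Schoenfeld power is Φ(|ln 0.645|·√(169.5/4) − 1.960) = 81.4%. The two unadjusted methods thus have nearly the same power. The open choice between them is a matter of prespecification and does not make a power shortfall.

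**Step 3: what adjustment could add.** For the adjusted marginal risk difference, the variance falls by about R², the share of outcome variance explained by baseline covariates. The saving is then about 1500 × R² patients, and power is as in step 2 with n = 750/(1 − R²). The documents give neither R² nor AUC, so I assume a range of AUC and convert it:

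- The score is distributed N(0,1) in patients without an event and N(d,1) in those with one, where d = √2·Φ⁻¹(AUC).
- Risk at score x is r(x) = p̄φ(x−d) / [p̄φ(x−d) + (1−p̄)φ(x)].
- R² = Var(r) / [p̄(1−p̄)], by numerical integration at p̄ = 0.113.

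| Assumed AUC | d | R² | Patients (of 1500) | Power at 1500 | Gain over 80.4% |
|---|---|---|---|---|---|
| 0.55 | 0.178 | 0.3% | 5 | 80.5% | 0.1 points |
| 0.60 | 0.358 | 1.3% | 20 | 80.9% | 0.5 points |
| 0.65 | 0.545 | 3.1% | 47 | 81.6% | 1.2 points |
| 0.70 | 0.742 | 6.0% | 90 | 82.7% | 2.3 points |
| 0.75 | 0.954 | 10.2% | 153 | 84.4% | 4.0 points |

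**Step 4: cross-check by simulation.** 6000 trials were simulated per setting, with 750 per arm and 13.6% against 9%. The standardised risk difference had variance ratios of 0.970, 0.946 and 0.905 at AUC 0.65, 0.70 and 0.75, equal to about 46, 81 and 143 patients. Type I error stayed near 5%. These figures agree with the table and are slightly lower. The standard error of a simulated power near 80% is √(0.8 × 0.2/6000) = 0.5 points, so differences of a few tenths mean little.

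**The case against.** A reader might infer that the primary analysis is an unadjusted chi-square test and that a definite number of patients' worth of precision is being thrown away. The documents do not support that reading.

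- **Cox regression.** The sentence on comparison between groups points to Cox, which can carry covariates, and nothing excludes them. The text leaves the primary method undetermined. This stands.
- **Prognostic strength.** No c-statistic, R² or covariate list is given, so any patient-equivalent is an assumption. Eligibility also narrows baseline risk: age is limited to 18–70, and confirmed hypertension, dialysis, hepatic impairment, bleeding diathesis and abnormal platelet counts are excluded. The composite mixes ischaemic events with bleeding, which may be hard to predict with one score. The low end of the range must therefore be taken seriously. This also stands.
- **Validity.** An unadjusted test is valid in a randomised trial, and the sample size was calculated for it. There is no bias and no shortfall against the stated power. This stands too.
- **Left to the analysis plan.** A covariate list is ordinary analysis-plan detail, and that plan is not shown, so its absence here is no fault. This carries only part of the way. For binary variables the article does not leave the method open: it fixes tests that cannot take covariates. An analysis plan that adjusted the primary binary endpoint would depart from that published choice.

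Adjustment also has limits. It deals with chance imbalance only in the covariates that are in the model.

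**Conclusion.** The point holds as an efficiency recommendation. Section {20a} sends the binary primary endpoint to tests that ignore baseline risk, names Cox as well, ranks neither and states adjustment for neither, while baseline data exist for every patient. The plan as written is valid and delivers its 80%.

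The likely gain is about 0.5 to 4 points of power, equal to about 20 to 150 of 1500 patients. It rests on an assumed AUC of 0.60 to 0.75 (about 1% to 10% of outcome variance explained), 1:1 allocation and the planned event rates. With weaker prediction it is near nil. The size applies to the marginal risk difference. An adjusted Cox or logistic coefficient is a conditional effect, and the R² formula does not carry over to it directly. It would be wrong to conclude that the trial is underpowered or that its test is incorrect.

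**What to change.** Before unblinding, state one primary analysis of the one-year composite: a logistic model with arm and a few baseline prognostic variables that are already recorded (for example age, sex and recorded clinical risk factors). Report it as the standardised one-year risk difference with 95% CI. This keeps the marginal contrast on which the trial was sized. Use the same covariates in the Cox model, labelled as secondary, and keep the unadjusted chi-square as a sensitivity analysis. With about 170 events expected (1500 × 0.113), a handful of covariates is supportable.

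The cost is a change of wording and minor analysis work. Data Availability says that data analysis had not begun, so the choice can still be prespecified. The downside is that the covariates must be fixed in advance, with a simple stated rule for occasional missing baseline values.
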